**7.3 Statistical significance, Generalizability and Power**

In order for this study to yield results that are statistically significant and are able to be applied to a population (i.e. generalizable), there needs to be adequate power and a sample size providing an accurate representation of the affected community. It has been determined that for generalizability and statistical significance, a minimum of 4 village pairs is required, with a sample size of 300 per village, with a village population of approximately 1000.

The following table shows the power calculations based on the above minimum considerations. The

table also shows these powers with varying degrees of the bovine effect on the village and the

percentage of the bovines that are actually treated.

Assumptions

- Design effect is 1.5, in other words the actual sample size is reduced by a factor of 1.5 to give an effective sample size. This reduction is due to the extra similarity within clusters that means the observations cannot be treated as independent.
- Assume an attrition rate between years 1 and 2 of 20%.
- Assume that years 1 and 2 are independent for the cumulative power.
- Target (net) sample size is the number obtained in each village for testing (after excluding non-compliers).
- Use a significance level of 1% year 1 and 5% year 2.
- This study works on treating the whole village.
- Assume a village size of 1000.

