### 1.3 Study Design

**Cluster Randomized Design:** We will select pairs of villages from identified communities (human prevalence 10-15%; bovine prevalence 10-15%) in Jiangxi province and Hunan province, with pairs being matched as closely as possible on factors related to transmission: i.e. infection levels, transmission ecology (e.g.: water height, flooding patterns), and force of infection (e.g.: water contact patterns, buffalo: human numbers, sanitation practices, herding practices). The trial will aim to select the villages that provide closest matching in pairs. Within each pair, one village will be randomly chosen as intervention (bovines treated twice annually) and the other will be a control. Annual mass treatment of residents will be carried out in both villages. The end-point for the trial will be human infection rates. The efficacy of bovine treatment will be measured by the accumulated comparison of human infection rates across intervention and control villages, and will be reflected in the predicted percentage of human infection-years prevented by the intervention. Human infection rates will be assessed at the end of each year for 4 years.

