###### Essential

- - The matched pairs are from the same province (i.e. 2 matched pairs from Hunan, 2 matched pairs from Jiangxi).
  - The human to bovine ratio is similar within the pair.
  - The prevalence and intensity of infection at baseline within humans and bovines (particularly Buffalo) are similar.
  - The ecology of the villages must be similar (e.g. climate, water height, flooding patterns (rainfall), vicinity to lakes and/or marshlands).
  - Grazing of the bovines is within their village.
  - The villages are sufficiently isolated from one another.
  - Water contact patterns are similar.
  - No boat harbors within the village, where fishing boats frequently visit leading to the contamination of marshland by defecation of infected fishermen.

Desirable

- - Village layout and geographical size are similar.
  - Occupations of residents are similar.
  - Sanitation practices are similar.
  - Herding practices are similar.

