# Table of sample size (no new villages)

| Bovine effect size &  % Bovines treated | # Paired villages | Target sample size per village | Power %  (Year 1) | Power %  (Year 2) | Cumulative power  (Yrs 1 & 2) |
| --- | --- | --- | --- | --- | --- |
| 60% & 70% | 4 | 300 | 26.7 | 80.3 | 89.5 |
| 60% & 80% | 4 | 300 | 38.1 | 88.7 | 95.7 |
| 60% & 90% | 4 | 300 | 51.3 | 94 | 98.5 |
|  |  |  |  |  |  |
| 70% & 70% | 4 | 300 | 38.2 | 90.1 | 96.2 |
| 70% & 80% | 4 | 300 | 53.3 | 95.5 | 98.9 |
| 70% & 90% | 4 | 300 | 68.6 | 98 | 99.8 |
|  |  |  |  |  |  |
| 80% & 70% | 4 | 300 | 50.9 | 95.7 | 98.9 |
| 80% & 80% | 4 | 300 | 68.0 | 98.4 | 99.8 |
| 80% & 90 % | 4 | 300 | 82.7 | 99.4 | 100 |

Target sample size per village corresponds to the number of villagers sampled (not necessarily all those exposed). Powers are based on adjusting the sample size per village for attrition and a design effect.

- 1. **Analysis Plan**

Initial descriptive statistics will be performed to examine an overall trend in the data. This will be followed by the calculation of the outcome measures. These outcome measures will then be compared across control and intervention villages in order to determine the efficacy of the intervention. The empirical data gathered in this study will be put into the previously developed mathematical model (Williams *et al* 2002) in order to validate its predictions. Microsoft Access will be used for Data Management and SAS will be used for Data Analysis.

1. **Ethics**

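### The power table in section 7.3 shrinks only the person count and makes no allowance for having just 4 randomised village pairs, so its single-year powers are too favourable

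*Protocol*

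**What the plan says.** The randomised unit is the village. Section 1.3 states: "Within each pair, one village will be randomly chosen as intervention". The Essential list in section 4.1 fixes the number of pairs: "2 matched pairs from Hunan, 2 matched pairs from Jiangxi", so 4 pairs and 8 villages.

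Section 7.3 says that "for generalizability and statistical significance, a minimum of 4 village pairs is required". It sets the sample at 300 persons in each village and takes villages to have about 1000 residents. Its clustering assumption is: "Design effect is 1.5, in other words the actual sample size is reduced by a factor of 1.5 to give an effective sample size". It also assumes 20% attrition between years 1 and 2, and significance levels of 1% in year 1 and 5% in year 2. The note under the power table says what lies behind the figures: "Powers are based on adjusting the sample size per village for attrition and a design effect".

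Section 7.3 gives no control-arm infection rate, no sidedness and no test.

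**The concern.** A design effect corrects the variance of the comparison for similarity within villages. It does not correct for that variance being estimated from very few villages. With 4 pair differences the reference distribution is t with 3 df, whose two-sided critical values are 3.18 at 5% and 5.84 at 1%; the normal values are 1.96 and 2.58. If the table used normal critical values, it gives powers that a village-level analysis of this design does not have.

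The table is the only quantitative support for the number of clusters. If its powers are too high, a null result could be read as stronger evidence against bovine treatment than it is. A person-level analysis chosen to match the table would overstate the strength of a positive result.

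**Working it through.** **Inputs.** From section 7.3: 4 pairs, 300 persons per village, design effect 1.5, 20% attrition, levels of 1% (Year 1) and 5% (Year 2), and the nine printed rows. Assumed: two-sided tests, because sidedness is not stated.

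**1. Reproducing the table.** Effective persons per arm are 4 × 300 / 1.5 = 800 in Year 1 and 800 × 0.8 = 640 in Year 2. The intervention rate is taken as control rate × (1 − effect × coverage). The control rate is not given, so it was scanned.

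- Year 2: a two-sided normal test with an assumed control rate of 9.75% comes within 1.8 points of all nine rows (first row 78.7 against 80.3).
- Year 1: control rates of 10-15%, the village-selection range in section 4.1, give 70.5-90.8% for the first row against 26.7% printed. The best fit needs about 4% and still misses by up to about 4 points.

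The table is therefore not fully reproduced.

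**2. Which reference distribution was used.** Combining the printed columns as 1 − (1 − P1)(1 − P2) gives 1 − 0.733 × 0.197 = 85.6% in the first row, against 89.5% printed. Now re-express Year 1 at 5% with a normal reference. The implied noncentrality is 2.576 + z(0.267) = 1.954, power at 5% is Φ(1.954 − 1.960) = 49.8%, and the combination is 1 − 0.502 × 0.197 = 90.1%. Done this way, all nine cumulative values return within 0.6 points. The same exercise with a t reference misses by up to 2.6 points (6 df) or 4.6 points (3 df). Together with the note under the table, this points to a normal reference with no small-cluster correction.

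**3. Recalculating with village-level degrees of freedom.** The noncentrality implied by each printed power, 2.576 + z(P1) or 1.960 + z(P2), is kept, so the effect and the 1.5 are unchanged. First row, Year 2: 1.960 + 0.852 = 2.812. Last row, Year 2: 1.960 + 2.512 = 4.472. Power is then read from the noncentral t. Critical values are 3.182 and 5.841 on 3 df, and 2.447 and 3.707 on 6 df, at 5% and 1%.

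| Effect / coverage | Year 1 printed | 3 df | 6 df | Year 2 printed | 3 df | 6 df |
|---|---|---|---|---|---|---|
| 60 / 70 | 26.7 | 7.2 | 13.3 | 80.3 | 48.6 | 65.2 |
| 60 / 80 | 38.1 | 9.7 | 18.9 | 88.7 | 57.5 | 75.3 |
| 60 / 90 | 51.3 | 12.9 | 26.0 | 94 | 65.5 | 83.2 |
| 70 / 70 | 38.2 | 9.7 | 18.9 | 90.1 | 59.3 | 77.2 |
| 70 / 80 | 53.3 | 13.4 | 27.2 | 95.5 | 68.6 | 85.9 |
| 70 / 90 | 68.6 | 17.9 | 37.3 | 98 | 75.8 | 91.4 |
| 80 / 70 | 50.9 | 12.8 | 25.8 | 95.7 | 69.0 | 86.3 |
| 80 / 80 | 68.0 | 17.7 | 36.8 | 98.4 | 77.4 | 92.4 |
| 80 / 90 | 82.7 | 23.8 | 49.8 | 99.4 | 83.4 | 95.8 |

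Every printed Year 2 power is above 80%. On 3 df, eight of the nine fall below it; on 6 df, three do.

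**4. Randomisation test.** Four pairs give 2^4 = 16 allocations, so the smallest two-sided p is 2/16 = 0.125.

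**5. Design effect.** At 300 per village, 1.5 implies an ICC of 0.5/299 = 0.0017. It is held fixed throughout, because the protocol gives no other value.

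**The case against.** **The trial accumulates years.** Sections 1.3 and 7.1 measure efficacy by an accumulated comparison with yearly assessments for 4 years, and section 3.1 plans one interim analysis, after year 2, by Bayesian methods. A single-year power is therefore not the power of the trial, and no Year 1 decision is described. This stands. As an illustration, assume 20% attrition every year, a constant effect, fully persistent between-village variance and independent sampling error between years. The Year 2 variance is proportional to 1.5/240 = 0.00625, with an ICC of 0.5/239 = 0.00209. Over two years there are 300 + 240 = 540 person-years, and the variance is 0.00209 + 0.99791/540 = 0.00394. In the first row the noncentrality becomes 2.812 × √(0.00625/0.00394) = 3.54, so 3-df power is about 66%. Over four years (885.6 person-years) it is about 74%. The 70/80 row gives 85% and 91%, and the 80/90 row 95% and 98%.

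**Coverage.** Section 5.2 requires 100% bovine coverage, yet the table stops at 90%. At 100%, with the assumed control rate of 9.75%, single-year 3-df power in Year 2 is about 79%, 90% and 97% for effects of 60%, 70% and 80%. A reader might infer from the 3-df column that the trial could not show the effect. These two points are why the documents do not support that.

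**No test is named.** The 3 df presuppose a pair-level analysis, and the choice may be made in a statistical analysis plan not shown here. Hence the 6-df column, which still lies below every printed figure. A reader might also infer from the 0.125 floor that 4 pairs can never reach 5%. The floor binds only an exact randomisation test, which the protocol does not specify; a t-test can reach 5%. The sentence in section 7.3 also calls 4 pairs a required minimum, not a guarantee.

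**The normal reference is inferred.** This is correct. From the Year 2 column alone, a 3-df calculation with another control rate would also fit. The cumulative column separates the two, but only if Year 1 enters at 5%, against the stated 1%.

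**The size of the design effect.** It is tempting to argue that 1.5 is too small. Matching on prevalence, ecology and water contact should reduce within-pair variation, and the protocol gives no figure from which a larger ICC could be derived. The results above do not depend on that argument.

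**Conclusion.** The point holds for the printed single-year powers. Section 7.3 adjusts persons for clustering and attrition but describes no allowance for 4 randomised pairs. With its own implied effects and design effect, Year 2 power is 48.6-83.4% on 3 df or 65.2-95.8% on 6 df, against 80.3-99.4% printed. Year 1 power is 7.2-23.8% or 13.3-49.8%, against 26.7-82.7%.

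This rests on two-sided tests, on a normal reference behind the printed powers (supported by the note under the table and the cumulative column, though not stated), and on noncentralities backed out of those powers. The Year 1 figures are the less secure, because that column could not be reproduced at the prevalences the protocol gives. It is not shown that the trial is unable to detect the effect.

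**What to change.** - Recompute the power table for a village-level or pair-level analysis with the matching degrees of freedom, for the accumulated comparison as well as for single years. State the control rate, the sidedness and the level used in each column.
- Show the powers over a range of design effects or within-pair ICCs, labelled as an assumption.
- Reword the sentence linking 4 pairs to statistical significance, so that it does not suggest the number of pairs secures it. If an exact randomisation test is to be used, state that its two-sided p cannot fall below 0.125.
- Rest the conclusion on the pair-level estimate with a t-based (3 df) confidence interval.

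The cost is a recalculated table and some protocol wording. The stated power becomes less favourable, but no villages need be added to state it correctly. Restoring the printed powers by design is a separate decision: with the same information per pair and a t-test on pairs − 1 df, about 7 pairs would be needed for Year 2 and 8 for Year 1.

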# Table of sample size (no new villages)

| Bovine effect size &  % Bovines treated | # Paired villages | Target sample size per village | Power %  (Year 1) | Power %  (Year 2) | Cumulative power  (Yrs 1 & 2) |
| --- | --- | --- | --- | --- | --- |
| 60% & 70% | 4 | 300 | 26.7 | 80.3 | 89.5 |
| 60% & 80% | 4 | 300 | 38.1 | 88.7 | 95.7 |
| 60% & 90% | 4 | 300 | 51.3 | 94 | 98.5 |
|  |  |  |  |  |  |
| 70% & 70% | 4 | 300 | 38.2 | 90.1 | 96.2 |
| 70% & 80% | 4 | 300 | 53.3 | 95.5 | 98.9 |
| 70% & 90% | 4 | 300 | 68.6 | 98 | 99.8 |
|  |  |  |  |  |  |
| 80% & 70% | 4 | 300 | 50.9 | 95.7 | 98.9 |
| 80% & 80% | 4 | 300 | 68.0 | 98.4 | 99.8 |
| 80% & 90 % | 4 | 300 | 82.7 | 99.4 | 100 |

Target sample size per village corresponds to the number of villagers sampled (not necessarily all those exposed). Powers are based on adjusting the sample size per village for attrition and a design effect.

- 1. **Analysis Plan**

Initial descriptive statistics will be performed to examine an overall trend in the data. This will be followed by the calculation of the outcome measures. These outcome measures will then be compared across control and intervention villages in order to determine the efficacy of the intervention. The empirical data gathered in this study will be put into the previously developed mathematical model (Williams *et al* 2002) in order to validate its predictions. Microsoft Access will be used for Data Management and SAS will be used for Data Analysis.

1. **Ethics**

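### The Year 2 power column in Section 7.3 does not follow from the Year 1 column under the listed assumptions, and the cumulative column does not follow from the two under the stated independence

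*Protocol*

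**What the plan says.** Section 7.3 states that "a minimum of 4 village pairs is required, with a sample size of 300 per village" and offers the table of sample size as the supporting power calculation. The assumptions that bear on the table are:

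- "Design effect is 1.5, in other words the actual sample size is reduced by a factor of 1.5 to give an effective sample size"
- "Assume an attrition rate between years 1 and 2 of 20" (per cent)
- "Assume that years 1 and 2 are independent for the cumulative power"
- "Use a significance level of 1% year 1 and 5% year 2"

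The "table also shows these powers with varying degrees of the bovine effect on the village and the" percentage of bovines treated. Each of the nine rows has one bovine effect, one treated percentage, four pairs and 300 people per village. The note below the table says: "Powers are based on adjusting the sample size per village for attrition and a design effect". The section lists no control infection rate, no effect by year, no test and no sidedness. The first row reads "60% & 70% | 4 | 300 | 26.7 | 80.3 | 89.5".

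**The concern.** Within a row, the listed assumptions change only two things between the years. Attrition lowers Year 2 power, and the looser significance level raises it. The printed jump, from 26.7% to 80.3% in row 1, looks far too large for the net result of those two.

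The case that four pairs of 300 are enough rests on the later columns. In Year 1 only the last row exceeds 80% power (82.7%), while in Year 2 all nine rows do. If the Year 2 and cumulative figures depend on something the Protocol does not state, a reader can neither check the sample size nor tell what must be true for it to suffice.

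**Working it through.** **Inputs.** From Section 7.3: significance level 1% then 5%; Year 2 sample equal to 0.8 of Year 1; design effect 1.5 in both years, so it cancels; one effect per row. The Year 1 column cannot be derived, because no control infection rate is listed, so I take it as given. It fixes the noncentrality, and no control rate is then needed for the step to Year 2. Two-sided tests are my assumption.

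**Year 2, row 1 (60% & 70%), normal approximation.**

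- Year 1 noncentrality: d1 = z(0.995) + z(0.267) = 2.576 − 0.622 = 1.954.
- After attrition, same effect: 1.954 × √0.8 = 1.748.
- Year 2 power: Φ(1.748 − 1.960) = 41.6%, against 80.3% stated.

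**Sensitivity, row 1.** One-sided tests give 45.2%. No attrition at all gives 49.8%. A paired t-test on four pairs (3 df), with the noncentrality solved from Year 1 power and scaled by √0.8, gives 61.3%, or 70.0% without attrition. None reaches 80.3%. On the normal scale, 80.3% needs a noncentrality of 1.960 + 0.852 = 2.812, which is 1.44 times d1. At the same effect that is about 2.07 times the Year 1 sample, whereas the plan assumes a 20% loss.

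**All rows (power, %).**

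| Row | Year 1 stated | Year 2 stated | Year 2 normal | Year 2 t, 3 df | Cumulative stated | Cumulative by stated rule | Cumulative, Year 1 at 5% |
|---|---|---|---|---|---|---|---|
| 60 & 70 | 26.7 | 80.3 | 41.6 | 61.3 | 89.5 | 85.6 | 90.1 |
| 60 & 80 | 38.1 | 88.7 | 52.9 | 75.5 | 95.7 | 93.0 | 95.7 |
| 60 & 90 | 51.3 | 94 | 64.5 | 87.0 | 98.5 | 97.1 | 98.4 |
| 70 & 70 | 38.2 | 90.1 | 53.0 | 75.6 | 96.2 | 93.9 | 96.3 |
| 70 & 80 | 53.3 | 95.5 | 66.2 | 88.3 | 98.9 | 97.9 | 98.9 |
| 70 & 90 | 68.6 | 98 | 78.2 | 95.7 | 99.8 | 99.4 | 99.7 |
| 80 & 70 | 50.9 | 95.7 | 64.2 | 86.7 | 98.9 | 97.9 | 98.9 |
| 80 & 80 | 68.0 | 98.4 | 77.7 | 95.5 | 99.8 | 99.5 | 99.8 |
| 80 & 90 | 82.7 | 99.4 | 88.2 | 99.0 | 100 | 99.9 | 100.0 |

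The Year 2 shortfall is 11.2 to 38.7 points by the normal approximation and 0.4 to 19.0 points by the t-test.

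**Order of the rows.** With a constant effect and the same test, Year 2 power increases with Year 1 power, so a row ahead in Year 1 must stay ahead in Year 2. Three pairs of rows break this:

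- 60 & 90 goes from 51.3 to 94, but 80 & 70 goes from 50.9 to 95.7.
- 70 & 80 goes from 53.3 to 95.5, against the same 50.9 to 95.7.
- 70 & 90 goes from 68.6 to 98, but 80 & 80 goes from 68.0 to 98.4.

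A common change of significance level, sample size or test cannot reverse these orders.

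**Cumulative column, row 1.** By the stated independence, 1 − (1 − 0.267)(1 − 0.803) = 1 − 0.733 × 0.197 = 85.6%, not 89.5%. If Year 1 is tested at 5%, its power is Φ(1.954 − 1.960) = 49.8%, and 1 − 0.502 × 0.197 = 90.1%. On that basis every row lies within 0.6 points of the printed value, and eight of the nine within 0.1.

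**The case against.** The strongest reply is that the human effect need not be the same each year. Treating bovines acts indirectly through transmission, Section 1.2 presents the work through a transmission model, and Sections 1.3 and 7.1 measure efficacy by an accumulated comparison. An effect that grows in Year 2 fits such a design. As an illustration, take effect × coverage as the relative reduction, calibrate the control rate to Year 1 (800 effective per arm) and square the relative risk in Year 2 (640 per arm). Rows 1 to 9 then give 85.1, 92.2, 96.2, 92.0, 96.4, 98.5, 95.7, 98.2 and 99.3, close to the printed column in most rows. This stands as a plausible explanation. It is not listed, however, and this simple version does not reproduce the order reversals, so it cannot be taken as what was done.

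It also stands that the size of the gap depends on the test. Under a 3-df t-test the top row is essentially met.

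Three stronger readings are tempting and are not supported:

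- A reader might infer that Year 2 pools both years, so that the cumulative column counts Year 1 twice. The stated independence points to separate-year data, and pooling at a constant effect could not reverse the row order.
- A reader might infer that the control rate would have to rise implausibly between years. That presupposes a constant relative effect, which is the point in question.
- A reader might infer that an inconclusive interim would be over-read. Section 3.1 (Stage 8) plans a Bayesian interim, not the 1% and 5% tests of the table, and if early termination is not possible the trial continues to 2008.

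**Conclusion.** The point holds as an inconsistency between the printed power figures and their own listed assumptions. It does not show that true power is low: either the Year 2 column is wrong, or an assumption specific to year and row is missing, and the Protocol does not show which.

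If the effect is constant, all nine rows no longer exceed 80% in Year 2. One does by the normal approximation, and six do by the 3-df t-test. The contradiction is firmest in the weaker-effect rows. These figures rest on taking the Year 1 column as correct, on two-sided tests and on noncentrality scaling with the square root of sample size. The order reversals need none of the computed power values.

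The cumulative error is separate and smaller, 3.9 points in row 1 and less in the other rows. It follows from the printed columns alone. That Year 1 was entered at 5% is an inference from the close match, not something the document states.

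**What to change.** Take one of two routes for Year 2. Either recompute the column from the listed assumptions, or add to Section 7.3 the control infection rate, the relative reduction assumed for each year and the test used (with its sidedness), so that the printed column can be reproduced. Then recompute the cumulative column from Year 1 at 1% and Year 2 at 5% under the stated independence. Restate the table, and claim no more power than it shows.

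The cost is a recalculated table and a few added assumption lines. Some powers will become less favourable. The design, the number of villages and enrolment do not change.

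### The cumulative two-year power in Section 7.3 does not follow from the printed yearly powers: the independence formula gives 85.6% in the first row, not 89.5%, and is below print in every row

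*Protocol*

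**What the plan says.** Two assumptions in Section 7.3 of the Protocol govern the last column of its sample-size table. The first fixes the test levels: "Use a significance level of 1% year 1 and 5% year 2". The second fixes how the years relate: "Assume that years 1 and 2 are independent for the cumulative power". No formula for the cumulative power is printed, and no third significance level is given.

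The table covers nine combinations of bovine effect size and percentage of bovines treated, each with 4 village pairs and 300 people per village. Each row gives Year 1 power, Year 2 power and cumulative power. The first row (60% effect, 70% treated) reads "26.7 | 80.3 | 89.5", the second "38.1 | 88.7 | 95.7" and the fourth (70% effect, 70% treated) "38.2 | 90.1 | 96.2". The note under the table says that attrition and the design effect are already allowed for in the powers.

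**The concern.** When two tests are independent and success means detecting the effect in at least one of them, the cumulative power is fully determined by the two yearly powers. The printed cumulative values are higher than that result in every row. Typing slips would scatter in both directions; nine differences the same way point to a rule other than the one a reader would take from the assumptions.

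The cumulative column is the table's summary of what 4 pairs of 300 can show over two years, and two years is when the interim analysis (Section 3.1, Stage 8) decides whether the project can end early. If the column is too high, the chance of missing a real effect by then is understated. It also matters that a reader cannot tell from the document which test the cumulative power refers to.

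**Working it through.** **Inputs.** P1 and P2 are the Year 1 and Year 2 powers as printed in the Section 7.3 table. The levels are 1% and 5%, with the years independent, from the assumptions list. Nothing else is needed for the first check. In particular, it does not depend on how the yearly powers were obtained.

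**Step 1: the independence formula.** Cumulative power = 1-(1-P1)(1-P2).

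| Row (effect & treated) | P1 | P2 | 1-(1-P1)(1-P2) | Printed | Printed minus computed |
|---|---|---|---|---|---|
| 1 (60% & 70%) | 26.7 | 80.3 | 1-0.733×0.197 = 85.6 | 89.5 | 3.9 |
| 2 (60% & 80%) | 38.1 | 88.7 | 1-0.619×0.113 = 93.0 | 95.7 | 2.7 |
| 3 (60% & 90%) | 51.3 | 94 | 1-0.487×0.060 = 97.1 | 98.5 | 1.4 |
| 4 (70% & 70%) | 38.2 | 90.1 | 1-0.618×0.099 = 93.9 | 96.2 | 2.3 |
| 5 (70% & 80%) | 53.3 | 95.5 | 1-0.467×0.045 = 97.9 | 98.9 | 1.0 |
| 6 (70% & 90%) | 68.6 | 98 | 1-0.314×0.020 = 99.4 | 99.8 | 0.4 |
| 7 (80% & 70%) | 50.9 | 95.7 | 1-0.491×0.043 = 97.9 | 98.9 | 1.0 |
| 8 (80% & 80%) | 68.0 | 98.4 | 1-0.320×0.016 = 99.5 | 99.8 | 0.3 |
| 9 (80% & 90%) | 82.7 | 99.4 | 1-0.173×0.006 = 99.9 | 100 | 0.1 |

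The printed figure is not reproduced in any row.

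**Step 2: can rounding explain it?** With both row 1 inputs at their upper rounding limits (26.75 and 80.35), the formula gives 1-0.7325×0.1965 = 85.61%. That is still well below 89.5%. Only row 9 could be a display choice, since 99.9 shown as a whole number is 100.

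**Step 3: one pooled test on both years.** Sidedness is not stated, so I assume two-sided tests and a normal approximation. In row 1 the printed powers imply noncentralities of 1.95 (Year 1, from 26.7% at 1%) and 2.81 (Year 2, from 80.3% at 5%). Two ways of combining them are:

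- Root sum of squares: √(1.95²+2.81²) = 3.42, which gives 92.8% at 5% (critical value 1.96) and 80.2% at 1% (critical value 2.576).
- Equal weights: (1.95+2.81)/√2 = 3.37, which gives 92.1% at 5% and 78.7% at 1%.

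None of these is 89.5%. Row 2 gives 97.1% to 97.4% at 5% and 89.9% to 90.7% at 1%, against 95.7% printed. So pooling at either stated level fails as well.

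**Step 4: what would come close?** Two rules do, and neither is stated in the document.

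- *Year 1 credited at 5% instead of 1%.* Moving each P1 to the 5% level under the Step 3 assumptions and applying the independence formula gives 90.1, 95.7, 98.4, 96.3, 98.9, 99.7, 98.9, 99.8 and 100.0. This is within about 0.1 point of print in rows 2 to 9 and 0.6 point off in row 1. Back-solving row 1 gives a Year 1 power of 1-0.105/0.197 = 46.7%, against 49.8% from the shift.
- *A pooled test at a level near 3%.* At 3%, the root-sum-of-squares version gives 89.5% in row 1 and is within about 0.2 point of print in all nine rows.

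The printed column therefore cannot identify its own rule, least of all in the rows near 100%, where the candidates converge.

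**The case against.** The strongest reply is that the Protocol never prints 1-(1-P1)(1-P2). Independence of the years is also what one would assume in order to pool them, and Sections 1.3 and 7.1 measure efficacy by an accumulated comparison of infection rates. On that reading, cumulative power would be the power of a pooled test and the formula in the table above would be the wrong benchmark. This stands in part: a pooled test is a legitimate intention, and the fix must leave room for it. It does not rescue the column, because a pooled test reproduces the print only at a level near 3%, and Section 7.3 gives 1% and 5% and nothing else.

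A reader might go further and infer that Year 1 was counted at 5%, so that the plan mixes two error rules and carries a larger false-positive risk than stated. The document does not support this. That explanation misses the first row by 0.6 point, the pooled alternative fits at least as well, and no passage proposes testing both years at 5%.

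It is also fair to say that the consequences are limited. Year 2 power alone is at least 80.3% in every row, and six of the nine gaps are 1.4 points or less.

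**Conclusion.** The point holds as an internal inconsistency: the printed cumulative powers do not follow from the printed yearly powers under the stated levels and the stated independence. It rests on the printed table and on reading cumulative power as detection in at least one of two independent years. The pooled reading at either stated level does not remove the inconsistency.

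On the independence formula, the chance of missing the effect over two years is 14.4% rather than 10.5% in row 1, 7.0% rather than 4.3% in row 2, and 6.1% rather than 3.8% in row 4. The cause cannot be determined from the document. The design is not overturned, since the lowest corrected value is 85.6%. Whether independence between years is realistic is a separate question; this discrepancy remains even if it is granted.

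**What to change.** Replace the cumulative column by 1-(1-P1)(1-P2) from the yearly columns at the stated 1% and 5% levels (85.6, 93.0, 97.1, 93.9, 97.9, 99.4, 97.9, 99.5 and 99.9) and print the formula under the table. If the sponsor intended another rule, such as a pooled two-year test, add that rule and its significance level to the assumptions in Section 7.3 and recompute the column from it. The cost is one table column and a sentence. Under the independence formula the stated power becomes slightly less favourable; the number of pairs, the 300 per village and the conduct of the trial are unaffected.
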